## Abstract

**Introduction:**

Individuals with spinal cord injury (SCI) can experience accelerated cognitive aging. Myokines (factors released from muscle cells during contractions), such as brain-derived neurotrophic factor (BDNF), are thought to have beneficial effects on cognition. Neuromuscular electrical stimulation (NMES) was shown to elicit a large release of myokines. However, the effects of NMES on cognitive function have not been studied.

**Objective:**

To present the study protocol for a clinical trial evaluating the effects of NMES aimed at improving cognition and BDNF.

**Methods:**

A replicated randomized three-phases single-case experimental design (SCED) with sequential multiple baseline time series and a single-armed prospective trial will be conducted with 15 adults with chronic SCI (> 12 months after injury) above L1 neurological level undergoing 30-min quadriceps NMES, 3 days per week for 12 weeks.

**Main study endpoints:**

Primary endpoint is cognitive performance (assessed by a smartphone test) conducted three times per week during the baseline phase with random duration of 3 to 8 weeks, the intervention phase of 12 weeks, and the follow-up phase of 3 weeks after a no measurement rest period of 12 weeks. Secondary endpoints are changes in BDNF levels and cognitive performance measured before the baseline period, before and after intervention and after a 12 weeks follow-up.

**Conclusion:**

This will be the first study investigating the effects of 12 weeks NMES on both cognition and BDNF levels in individuals with SCI. The SCED results provide information on individual treatment effect courses which may direct future research.

**Trial registration:**

ClinicalTrials.gov (NCT05822297, 12/01/2023).

**Supplementary Information:**

The online version contains supplementary material available at 10.1186/s12883-024-03699-9.

## Introduction

Cognitive problems in persons with spinal cord injury (SCI) have long been underrecognized and were usually explained by concomitant traumatic brain injury (TBI). However, since less than five years, it has been noted that individuals with SCI suffer from accelerated cognitive aging, even when correcting for mood factors and in the absence of TBI [1–4]. Individuals with SCI face a 13-fold increase in the risk of cognitive impairment compared to the general population [5] and they are twice as likely to develop Alzheimer’s dementia [6–8]. The cognitive domains most affected following SCI are executive functions, long-term memory, short-term memory, attention [2], processing speed and verbal fluency [1] when controlling for mood factors. This cognitive impairment begins in the subacute phase and seems to worsen over time [9]. It was found that individuals with SCI have cognitive impairments and brain activation patterns that are similar to healthy adults that are on average 20 years older [1, 10]. A proposed mechanism for this cognitive decline is neuroinflammation [4, 11]. Neuroinflammation plays a role in normal age-related cognitive decline [12–14] and following spinal injury, chronic elevation of neuroinflammation is found in the whole central nervous system [15–17].

Physical exercise interventions have been shown to have anti-inflammatory effects, induce an elevation of neurotrophic factors in the bloodstream, potentiate neuroplastic processes in the brain, increase brain volume and benefit cognitive function [18–21]. The anti-inflammatory effect and increase in neurotrophic factors during exercise results in part from the release of products from contracting muscle cells (i.e. myokines) [20]. This release of myokines has been reported following all sorts of muscle training, including electrical stimulation [20, 22]. It is often difficult for persons with SCI to sufficiently engage in physical exercise, with only 50% of SCI patients engaging in any leisure-time physical activity at all [23]. This difficulty may depend on the level of injury and the severity of motor function loss, as well as the availability of sport opportunities for wheelchair users. Electrical stimulation has been proposed as an interesting addition or alternative for increasing circulating myokine levels in humans with difficulty to participate in regular exercise programs [22]. Electrical stimulation can be used alone, i.e. neuromuscular electrical stimulation (NMES), or to assist voluntary exercise, i.e. functional electrical stimulation (FES). NMES induces contraction of myocytes similarly to exercise, which results in the release of myokines in the circulation, as recently reviewed by Sanchis-Gomar et al. (2019) [22]. A widely studied myokine is brain-derived-neurotrophic factor (BDNF), which is released from neurons [24], astrocytes [25], platelets [26], and skeletal muscle [27] and can trigger neuroprotective and neurotrophic effects [28]. Some studies suggest that most of the circulating BDNF is released from the brain [29]. Some other myokines, like insulin-like growth factor-1 and irisin were suggested to induce the release of brain-derived BDNF [20]. Remarkably, one study in young healthy adults reported that circulating levels of the myokine named BDNF increased more following a single bout of NMES than voluntary exercise with the same integrated force of muscle contraction [30]. Similarly, in a rat study, assessing able-bodied rats, the increase in BDNF levels was two times higher after four weeks of NMES compared to four weeks of running [31]. Also in human studies, long-term interventions with NMES were reported to increase circulating levels of BDNF, for example in older adults with type 2 diabetes [32]. BDNF can be considered one of the most important exercise-induced factors as it has direct beneficial effects on synaptic plasticity and neurogenesis, and it was linked with brain atrophy and cognitive function in a wide array of research [33]. So far, however, we were unable to find any studies reporting a beneficial effect of NMES on cognitive function. To the best of our knowledge, only one other study has evaluated the effects of FES [34] and only one study evaluated the effects of NMES [35] on cognitive function. The FES study is also the only study investigating exercise effects on cognition in SCI patients. In this study, improvements on a working memory task were reported after 6 months of functional electrical stimulation (FES)-assisted rowing exercise in SCI patients. This study did not measure myokine levels [34]. The authors of the NMES study evaluated the effect of a short intervention of 15 days of NMES in coronary bypass patients and discovered that patients in the experimental group showed increases in functional connectivity in the brain frontoparietal, salience and sensorimotor networks [35]. Overall, there is a lack of knowledge on the effects of electrical stimulation to improve cognitive function and the dose–response needed to attain such effect.

We will use a randomized replicated ABC single case experimental design (SCED) [36]. Primarily, we will examine to what extent and after how many weeks a 12 week intervention with NMES may change performance of people with SCI on the momentary digital symbol substitution task, an information processing task that will repeatedly be administered via a smartphone application. NMES will be applied to the quadriceps muscles of individuals with SCI. An intervention of 12 weeks is considered to be sufficient to induce both a myokine response and muscular changes. Secondarily, we will assess changes in the myokine BDNF before and after the 12 week intervention with NMES and after a 12 week follow-up without NMES. We hypothesize that NMES will have a beneficial effect on cognitive performance starting from the first weeks and that 12 weeks of NMES will induce an elevation of BDNF levels. This study tests a new treatment strategy, accessible even to individuals with low physical exercise possibilities, with the potential to slow down or prevent further cognitive decline in persons with SCI. The explorative findings may guide future research. Furthermore, it may help to raise awareness of the process of accelerated cognitive decline in persons with SCI.

## Methods

The Standard Protocol Items: Recommendations for Interventional Trials (SPIRIT) guidelines (see Appendix) and RoBiNT scale for risk of bias in SCED studies were used in designing and describing this clinical trial [37, 38].

The trial was registered with ClinicalTrials.gov (NCT05822297) on the 12th of January 2023, sponsored by Adelante Zorggroep and approved by the Medical Ethical Testing Committee (reference number W23.071) of Maxima Medical Center at Veldhoven, the Netherlands on the 9th of October 2023. In case of important protocol modifications, they will be notified to the Medical Ethical Testing Committee and updated in the trial registry.

### Participants

Participants and recruitment: Participants will be recruited from the outpatient clinic of the rehabilitation center Adelante Centre of Expertise in Rehabilitation and Audiology, locations Hoensbroek and Maastricht University Medical Center (MUMC +)., the Netherlands. The rehabilitation physician will inform potential participants about the study and flyers with information will be handed over. The flyers will include the contact details of one of the researchers. Alternatively, participants can give permission to the physicians that their contact information can be sent to the researchers.

Inclusion criteria: Participants are eligible if they are 18 years or older, have SCI since at least one year (chronic phase), the injury level is L2 or higher (meaning that the quadriceps muscle is likely affected to some extent, since this muscle is innervated by radicular nerves L3-L4), completeness of injury has been scored according to the American Spinal Injury Association (ASIA) Impairment Scale (AIS) [39] as either A, B or C, if they are able to use apps on their smartphones, if they are able to use NMES device safely at home, and if they speak Dutch at a native level. We will exclude participants if we cannot induce visible or palpable contractions of the quadriceps muscles with NMES or if they cannot tolerate the NMES intervention. We will exclude participants with a diagnosis of cancer, neurodegenerative or psychiatric disorders, current pressure ulcers, a history of severe autonomic dysreflexia (systolic blood pressure elevations above 200 mmHg), have metal implants in the stimulation site, an intrathecal baclofen pump, or are currently pregnant. Finally, we exclude participants who have taken part in a program with electrical stimulation in the last 6 months prior to the study.

### Study design and procedures

#### Study design

This study will apply a randomized replicated sequential ABC single-case experimental design (SCED), with a baseline (A), intervention (B) and follow-up (C) phase [36, 40]. SCED study designs demonstrate strong internal validity to determine the likelihood of a causal relationship between the intervention and outcomes. One entity is observed repeatedly over a certain time period under different levels of at least one independent variable. The power in SCEDs is related to the number of data points for each participant and not the number of participants. Each participant serves as his/her own comparison, thus controlling for confounding variables that can impact outcome and allowing heterogeneous clinical presentations. The internal validity of the SCED results can be improved by randomization techniques such as randomization of the starting time of the intervention. The downside is that the generalizability of the study results to the total population still depends on the number of participants included (i.e. replication of the findings) [40, 41]. The SCED lend itself perfectly to reflect on the reasons for the (likely) variability in the onset of NMES-induced effects on cognitive performance, looking at individual participant’s intervention courses. Thus, allowing to reflect on the existence of different potentially moderating characteristics. Several potential moderators have been suggested previously [4] and will be measured within this study. These include concomitant traumatic brain injury, psychological alterations, chronic pain, hemodynamic dysregulation, level of injury, respiratory failure, substance (ab)use, educational level, cardiovascular diseases, and intensive care admission [4]. In addition, a SCED design allows us to interpret after how many weeks the NMES leads to changes in performance on the momentary digital symbol substitution task. The aforementioned advantages of SCED studies indicate how this design offers additional information that is well fitted for an explorative study in a new topic.

In the context of SCED studies, randomization does not refer to individuals being randomly allocated to treatment groups, but to the random onset of the intervention phase which is usually set within a fixed window of time in order to make this randomization more feasible [38]. In this study, a window of 9 to 24 measurement points (i.e. 3 to 8 weeks at the set frequency of three test assessments per week) will be employed in which the change of phase from baseline to intervention phase will be randomly determined. This determination will be done with a random number generator in Excel set to give a random number between 9 and 24. There will be a baseline phase ranging from 3 to 8 weeks, followed by an intervention phase of 12 weeks and a final follow-up phase of 3 weeks after a 12 week rest period with no measurements and no interventions. As we will exclude the first 4 measurements in the baseline phase from analysis, see Sect. "Statistical analysis", this leaves us at least 5 measurement points in this phase, 36 measurement points in the intervention phase and 9 measurement points in the follow-up phase. Neither participants nor researchers will be blinded to the phase of the intervention. Replication of the experiment will be done in 15 participants.

Finally, additional measurements will be done in a repeated manner according to a single-armed prospective design before baseline phase, at the end of the baseline phase, at the end of the intervention phase and at the start of the follow-up phase.

#### Study procedures

The experimental design is illustrated in Fig. 1. Upon the first appointment (T1), participants will sign an informed consent and undergo baseline examinations consisting of questionnaires and clinical tests. A smartphone application for repeated monitoring of cognitive function will be installed on their smartphones and they will be familiarized with the cognitive tests and neuromuscular electrical stimulation intervention. On a separate day (T2), within seven days from the first appointment, they will undergo a series of cognitive tests and venous blood samples will be collected. Furthermore, they will fill in a second list of questionnaires and undergo a clinical evaluation of strength and spasticity. This will be followed by a no-treatment baseline period with a random length of 3–8 weeks. Upon the third (T3), fourth (T4) and fifth (T5) visit, the oral cognitive tests, venous blood sample collection and questionnaires from T2 will be repeated. During the third visit (T3) the participants will receive their own NMES device for home-based training and they will be asked to return it 12 weeks later on the fourth visit (T4). All participants will undergo the same intervention. During the fourth visit (T4) the clinical evaluation of strength and spasticity that was done at T2 will be repeated. Between T2 and T4 and between T5 and T6 participants will undergo smartphone cognitive tests 3 times per week. At the end of the study, no additional tests will be done. Participants will be requested to write in a diary the specifications of the NMES session (duration, intensity) after each session and indicate when they performed a cognitive test. They can also write down any problems they encountered using the NMES device or smartphone application. Participants receive a telephone call once a week by one of the researchers to assess how they feel, be reminded of the diary and to assure there are no technical issues with the NMES device or smartphone application. Participants are allowed to withdraw from the study at any time. Available data from these participants will be included in the data analyses whenever possible.

**Fig. 1 Fig1:**
[figure not shown]
Experimental design. T1-5 represent measurement time points. During T2-5 the same measurements are repeated, expect the addition of clinical examination in time point T4. The red line is the expected change in cognitive test performance on the smartphone-based cognitive test without intervention, which we expect to show a fast increase in the first ± 3 sessions followed by a slight increase over time due to a learning effect. The X’s mark how cognitive test results are hypothesized to change due to the intervention

### Intervention

The intervention consists of 12 weeks NMES which will be done using the Pierensymphony M, serie A, article number 104800 (10,003,566) (manufactured by Pierenkemper GmbH and distributed by schwa-medico Nederland B.V.), a two-channel NMES device designed, and CE marked for muscular electrical stimulation (CE 0482). After a familiarization session, the intervention will be home-based, three times a week, with at least 1 day between stimulation sessions and 2 days between a stimulation session and testing day. Electrical stimulation will be done on the quadriceps muscles of both legs simultaneously. For each leg, one electrode is placed on the proximal lateral side and one on the distal medial side of the quadriceps muscle (see Fig. 2). Electrical stimulation will take 30 min, at a stimulation frequency of 50 Hz, and a pulse width of 400 μs. We will choose the highest intensity that is easily supported by the participant without inducing discomfort with a maximum intensity of 100 mA. We should at least see a visible or palpable contraction or the participant will be excluded. The activation within the activation-rest cycle consists of a 1 s ramp-up, 7 s full activation and 1 s ramp-down, followed by 18 s rest. Every 4 weeks the rest period will be diminished with 3 s until the rest phase is equal to the activation phase (9 s). Participants may continue their normal treatments, which may consist of physiotherapy. However, they will be asked not to change their physical activity habits during the experiment.

**Fig. 2 Fig2:**
[figure not shown]
Placement of the electrodes on the quadriceps muscles

### Cognitive assessments

#### Smartphone-based cognitive assessment

To study the primary aim of our study, participants will undergo a cognitive test for 3 times a week during the baseline, intervention and follow-up phase of the experiment. This repetitive cognitive test will be administered using a secured smartphone application, which was designed for use in clinical settings and research (m-Path, https://m-path.io/landing/). It will be programmed to emit an auditory signal three times a week signaling the availability of a new cognitive test between 7.30 AM and 10.30 PM on the days that participants do not undergo NMES sessions. The test is the momentary digital symbol substitution task, which is a measure of processing speed and short-term working memory function. For this test, participants have 30 s time to complete as many trials as possible where they need to correctly select the figure representing the number given as depicted in the legend provided on the top of the screen. The outcome is presented as response time derived from the number of trials/30 s (speed, in ms) and the percentage of correct trials (accuracy). Before the test starts, participants will be informed that they should be ready to respond as fast and accurate as possible. Daniëls et al. (2020) have validated this test for repeated use in healthy adults. They reported a significant learning effect for number of correct answers in 30 s between the first and 48th trial (B = 0.32, SE = 0.04, *p* < 0.001; with number of correct answers as the dependent variable and the logarithmic transformation of the session number (between 1 and 48) as the independent variable) [42].

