##### Randomization test

Subsequently, randomization tests will be performed to test the null hypothesis that NMES does not have an effect on participant’s cognitive function. The observations of the baseline phase will be compared to those of the intervention and follow-up phases respectively. The test statistic “means of phase A minus means of phase B” will be chosen as the primary outcome of this study. In case visual analysis suggests delayed effects, the randomization test will be repeated with lagged data until the lowest p-value has been reached (one effect lag equals one day). The first 4 measurements in the baseline phase will be removed before calculating the means, since we expect a learning effect on the first trials, leaving between 5 and 20 measurement points depending on the randomly decided length of the baseline period. Studies that tested the statistical properties of a randomization test used in this type of design showed that the Type I error probability of the randomization test was maintained at an acceptable level [61].

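### Test day and clock time of the primary smartphone test are not held comparable across phases, because the rule against testing on NMES days can bind only in phase B

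*Protocol article*

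**What the plan says.** The primary endpoint is a 30-second timed symbol-substitution task on the participant's own phone. Under Smartphone-based cognitive assessment, "participants will undergo a cognitive test for 3 times a week during the baseline, intervention and follow-up phase of the experiment". The app signals each test, "signaling the availability of a new cognitive test between 7.30 AM and 10.30 PM on the days that participants do not undergo NMES sessions".

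NMES is given only in phase B. Study procedures says of phase A: "This will be followed by a no-treatment baseline period". The device is handed back at T4, and Study design describes phase C as "a final follow-up phase of 3 weeks after a 12 week rest period with no measurements and no interventions". The Intervention section sets NMES at "three times a week, with at least 1 day between stimulation sessions and 2 days between a stimulation session and testing day".

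On blinding, Study design says: "Neither participants nor researchers will be blinded to the phase of the intervention". The Randomization test section takes "means of phase A minus means of phase B" as the primary statistic. The Single-case data sections give no role to clock time or day of the week. Study procedures does ask participants to keep a diary in which they "indicate when they performed a cognitive test", but no analysis of those entries is stated.

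**The concern.** A single-case design compares a person with himself or herself. That removes stable characteristics. It does not remove test conditions that change when the phase changes. Here one rule about test conditions takes effect at the moment NMES begins: days that were open for testing in phase A become closed in phase B. The hour is free within a long span in every phase, and the participant knows which phase is running. Three home sessions a week could also rearrange the times at which people are free to test.

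Randomising the start protects against influences whose timing is unrelated to the start. It cannot separate NMES from anything else that starts with NMES. If test days or hours moved at that point, and if performance depended on them, the difference would be read as an NMES effect. Even with no systematic move, hour-to-hour variation adds noise to a baseline mean that may rest on only 5 retained points.

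**Working it through.** **Schedule in the article.** Phase A has 9 to 24 tests, phase B 36 and phase C 9. The totals are 9 + 36 + 9 = 54 and 24 + 36 + 9 = 69, which reproduces the stated 54–69.

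**Width of the span.** 22.5 − 7.5 = 15.0 hours, the same in all phases.

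**Permitted test days.**
- Phases A and C have no NMES, so all 7 days are open: C(7,3) = 35 ways to place three tests.
- Phase B has three sessions a week, leaving 7 − 3 = 4 open days: C(4,3) = 4 ways.
- Seven repeating weekly patterns satisfy at least one day between sessions. In every one of them, each open day is adjacent to a session day. Three of the four open days come 1 day after a session and the fourth comes 2 days after.

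Two things follow. Four open days are enough for three tests, so unchanged test days are feasible: tests on Tuesday, Thursday and Saturday fit with NMES on Monday, Wednesday and Friday. But if the testing day in the Intervention section includes smartphone test days, the two-day spacing cannot be met with three sessions and three tests a week.

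**Bias, if a shift occurred.** The documents give no time-of-day effect, so both inputs are assumptions.
- Bias = (change in the share of tests taken at the better time) × (difference between better and worse times).
- Share moves from 50% to 75%, difference 0.5 within-person SD: 0.25 × 0.5 = 0.125 SD.
- Every test moves from worse to better: 1 × 0.5 = 0.5 SD, the extreme case under that assumption.

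**Effect on the randomization test.** This was simulated with 16 possible starts (9 to 24), the first 4 baseline points dropped, 36 phase B points, independent normal errors, a one-sided test, no true NMES effect and 5,000 runs per row. The smallest attainable p is 1/16 = 0.0625. (The Sample size calculation section counts 20 permutations; that is a separate matter.)

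| Phase-linked shift (SD, assumed) | Share of participants with p ≤ 0.0625 |
|---|---|
| 0 | about 6% |
| 0.25 | about 10% |
| 0.5 | about 14% |
| 1.0 | about 26% |

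**Noise.** Ignoring autocorrelation, in within-person SD units:
- 5 baseline and 36 intervention points: √(1/5 + 1/36) = 0.477.
- 20 and 36 points: √(1/20 + 1/36) = 0.279.
- If time of day explained 10–30% of within-person variance (assumption) and were held completely fixed, the factors are √0.9 = 0.949 and √0.7 = 0.837, a reduction of 5–16%. The first SE would become 0.453 to 0.399.

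**What a missed test costs.** With 4 rather than 5 baseline points, √(1/4 + 1/36) = 0.527, about 10% above 0.477. Combined with the gain, the SE is 0.527 × 0.949 = 0.500 at the 10% end (worse than 0.477) and 0.527 × 0.837 = 0.441 at the 30% end (still better). One lost baseline test can therefore cancel the gain or halve it.

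**The case against.** A reader might infer that phase B tests do fall on different days or at different hours, so that the primary contrast is biased. The documents do not support that. The hours and the test frequency are the same in every phase, and nothing ties clock time to phase. Because a test never shares a day with a session, NMES does not push the test to another hour of the same day. Home sessions can be fitted around unchanged test days. The sentence may also describe when the signal can sound rather than how long the test stays open; if the app sets the moment, the scope for an unblinded participant to choose a favourable one shrinks considerably. These points stand, and they rule out any claim of demonstrated bias.

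It can also be said that signal times and weekdays are operational detail that a condensed article leaves to the full protocol. That is fair for the missing same-hour rule taken alone. It does not dispose of the rule that the article does state, which restricts days in one phase only.

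There are partial safeguards: diary entries of when tests were done, weekly telephone calls, and a request not to change physical activity habits. They make a check possible, but no check is described. Finally, every effect size above is assumed, and the 0.125 SD bias is about a quarter of the 0.477 SD standard error for the shortest baseline (0.125 / 0.477 = 0.26).

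**Conclusion.** The point holds as a weakness in the stated test schedule, not as evidence of a biased result. The article allows a 15-hour span and a day restriction that can bind only in phase B (4 open days against 7), with unblinded participants and a raw difference in phase means. Comparability of test day and hour is therefore left to chance and habit.

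The main expected cost is noise. At most 5–16% of the standard error could be recovered, if time of day explains 10–30% of within-person variance and could be fully fixed; a wide time band would recover less. Phase-linked bias is possible, from 0.125 SD to an extreme of 0.5 SD under the assumed 0.5 SD effect, and the randomised start would not remove it. Whether any shift will occur, and how large it would be, cannot be learned from the documents. The change is worth making because it is cheap.

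**What to change.** - At T1, agree with each participant three test days that will stay free of NMES in phase B, and a usual time band such as morning, afternoon or evening.
- Programme m-Path to signal on those days and in that band in phases A, B and C, and say in the protocol whether the stated hours govern the signal or the period in which the test can be taken.
- Report the distribution of test times and days by phase, from app time stamps if they are kept and otherwise from the diary. Add a sensitivity analysis of the primary contrast that uses recorded test time.
- Reconcile the two-day spacing between a stimulation session and a testing day (Intervention) with the three-tests-a-week schedule (Smartphone-based cognitive assessment). It may refer to clinic visits only; the text should say which days it covers.

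The cost is an app setting, a few sentences and one extra analysis. The downside is possibly a few more missed tests. The randomized marker method handles these in the test but does not recover the information. The band should therefore be wide, and a hard lockout of two or three hours is not advised: with 5 retained baseline points, one missed test would offset much or all of the gain.
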